## 4 INTRODUCTION

The aim of volume replacement is to compensate a reduction in the intravascular volume e. g. during surgery and to counteract hypovolaemia in order to maintain haemodynamics and vital functions. Boldt (Boldt, 2005) concluded that volume replacement should not only tend to optimize macrocirculation and oxygen delivery but also to improve organ perfusion, microcirculation and inflammatory response.

Hydroxyethyl starch (HES) is the most intensively studied artificial colloidal plasma volume substitute (Boldt & Suttner, 2005). It consists of hydroxyethylated polymers of glucose, derived from amylopectin. The characteristics of HES can mainly be defined by the molecular weight and the molar substitution ratio, i.e. the ratio of replacement of glucose group by hydroxyethyl group during production. Various HES preparations exist showing different physico-chemical properties ((Jungheinrich & Neff, 2005),(Boldt & Suttner, 2005)). The Investigational Products Tetraspan® contain HES with an average molecular weight of 130,000 Daltons, a molar substitution of 0.42 and a substitution ratio of 6:1 is solved in a balanced electrolyte solution. The cation pattern in the crystalloid component Tetraspan® is adapted to physiological plasma electrolyte concentrations. The anion pattern is a combination of chloride, acetate and malate. The purpose is to minimize the risk of hyperchloraemia and acidosis. The additions of acetate and malate instead of lactate anions are intended to reduce the risk of lactic acidosis. In conclusion, Tetraspan® combines benefits of the modern 3. generation HES 130/0.42 with proven advantages of a balanced plasma adapted electrolyte solution.

While Tetraspan® 6% (containing 6% HES) is iso-oncotic, i.e. the increase in the intravascular plasma volume is equivalent (i. e. 100%) to the infused volume, the Investigational Test Product Tetraspan® 10% (containing 10% HES) is hyper-oncotic, i. e. the volume effect is 145%. Thus, a considerable intravascular effect could be achieved without overloading the interstitial compartment with fluid and consequently reducing oedema tendency with its known pathophysiological consequences ((Lobo *et al*, 2006), (Brandstrup, 2006)).

All products used in the present phase IV trial are registered in Germany as well as in various countries in Europe. The clinical use of the Investigational Products in the present study is within the approved Summary of Product Characteristics (SmPC).

## 5 STUDY RATIONALE

In elective pancreatic surgery intra- and postoperative volume replacement requirements are considerably high. With the administration of a hyper-oncotic colloid maintenance of haemodynamics and vital functions could be achieved more easily than with an iso-oncotic colloid or sole crystalloid therapy avoiding an fluid overload of the interstitial compartment which could lead to oedema tendency with its known pathophysiological consequences.

Elective pancreatic surgery is characterized by a highly standardized surgical, anaesthetic and postoperative care (SOP Dept. of Anaesthesiology and Intensive Care Medicine) and is well suited to compare the volume requirements following hyper-oncotic or iso-oncotic volume replacement therapy in comparison to crystalloid volume replacement alone. Individual intraoperative volume replacement therapy during surgery can be improved by target controlled replacement using oesophageal Doppler measurement as has been shown e. g. for abdominal surgery (Noblett *et al*. 2006, Wakeling *et al*. 2005).

## **6 RISK-BENEFIT-ASSESSMENT**

All Investigational Products are registered in Germany as well as in various European countries. The proposed use of the Investigational Products in the present study is in line with the registered SmPCs.

Goal-directed perioperative fluid therapy by determination of stroke volume has been found to reduce the risk of hypovolaemia or hypervolaemia and to reduce postoperative complications as well as length of stay in hospitals. This favours the use of individualized goal directed fluid and volume replacement therapy with oesophageal Doppler measurements (Review of the Agency for Healthcare Research and Quality Technology, 2007) instead of determining blood pressure alone as the ground for deciding volume administration.

Many of the proposed measures and parameters (laboratory, clinical) are performed/obtained routinely and thus, do not represent major additional burden to the patient.

In conclusion, the risk due to methods and measurements in the present study is considered to be low and a positive risk-benefit is assessed.

## **7 STUDY OBJECTIVES**

### **7.1 Primary Objective**

It is the primary aim of the planned study to investigate on the efficacy of target controlled fluid therapy with a hyper-oncotic compared to an iso-oncotic balanced HES 130/0.42 solution in adult patients undergoing elective pancreatic surgery.

#### **7.1.1 Primary Variable**

A multiple primary endpoint is defined which is “the intra-operative amount (in mLs) of colloidal volume replacement therapy during target directed volume replacement therapy” as the first primary endpoint and “days until fully on oral (solid) diet” as the second primary endpoint (full on oral diet is defined by the absence of parenteral and enteral nutrition and the patient is able to take oral nutrition for at least three times that day).

### **7.2 Secondary Objectives**

Secondary objectives are the investigation of safety and efficacy parameters like blood coagulation, perioperative blood loss, anastomotic or bowel leakage, renal function, haemodynamics, postoperative inflammation, intraabdominal pressure, adverse events and amount of given blood products (RBC, FFP, PC). Furthermore, descriptive comparison of the hyper- and iso-oncotic volume replacement therapy with HES to volume replacement therapy with a crystalloid alone will be made.

## **8 STUDY DESIGN**

This is a prospective, randomized, controlled, double-blind, multi-centre phase IV study performed in three parallel groups.

Comparison will be made of a hyper-oncotic (10%) balanced HES 130/0.42 solution with an iso-oncotic (6%) balanced HES 130/0.42 solution on the basis of a multiple endpoint. The principle of ordered hypothesis will be used [see section 16 statistics]

for testing the two primary endpoints: “the intra-operative amount of colloidal volume replacement therapy during target directed volume replacement therapy” (first), subsequently “days until fully on oral solid diet” (second).

A third treatment arm (as a descriptive control) will comprise the administration of solely a balanced crystalloid fluid replacement. This group is included in the study as in various hospitals and countries respectively volume replacement solely with electrolytes is still a standard in surgery including pancreatic surgery. As crystalloid solutions, however, display another volume effect\* than colloidal solutions (\*thus leading to to a distinct higher requirement of volume which could be easily recognised even when blinded) this treatment group will only serve as a descriptive control.

The study will be started with an internal pilot phase which serves for recalculation of sample size for the first primary variable respectively for ensuring sufficient power for the second primary variable. Interim analysis will also serve for deciding of premature termination of the study for futility. This interim analysis will be performed by estimating the pooled variances for both primary endpoints without unblinding [see section 16 statistics].

In the first phase of the study (internal pilot phase) the number of patients is 20 (including drop-outs) for each treatment arm.

Beside this two-phase design with a number of 60 patients in the pilot phase, a rough estimation of the sample size (for the 1st primary variable) to expect resulted in:

69 patients per group, supposing an effect size (difference of means)/(common standard deviation) =  $\frac{1}{2} = 0.5$ , error of the 1st kind  $\alpha = 5\%$  (two-sided), Power = 80% and the nonparametric Mann-Whitney U-Test (Calculations with nQuery Advisor, version 6.0). Taking a drop-out rate of 10% into consideration, a sample size of 76 patients per group will be needed.

This sample size also should be sufficient for the 2nd primary variable (for details see section 16)

Estimated total sample size:

Internal pilot phase

[figure not shown]

The study will be performed in three study centres in Berlin and Bonn, Germany.

\*\* may change according to calculation of pooled variance after internal pilot phase.

## **9 SELECTION AND WITHDRAWAL OF PATIENTS**

### **9.1 Informed Consent**

An informed consent, written in accordance with the origins of the Declaration of Helsinki (Appendix 1) and the applicable laws of the country has to be obtained from all patients.

The patient will sign the Informed Consent Form (Appendix 2) before s/he enters the study, i.e. before screening bloods, screening assessments or any other study-related activity. The Investigator will explain the nature, purpose and risks of the study including data confidentiality and protection aspects and provide the patient with a copy of the patient information (Appendix 2). The patient will be given sufficient time (preferably one day in advance) to consider the study's implications before deciding whether to participate.

Should there be any amendments to the Final Protocol, such that would directly affect the patient's participation in the study e.g. a change in any procedure, the Informed Consent Form must be amended to incorporate this modification and the patient's informed *re-consent* must be obtained.

### **9.2 Patient Inclusion Criteria**

The following inclusion criteria apply:

- Male or female patients  $\geq 18$  years of age and  $\leq 80$  years of age. Women of child bearing potential must test negative on standard pregnancy test (urine).
- Patients scheduled for undergoing planned elective surgery of the pancreatic head
- Patients who are willing to give of voluntary consent to participate in the study, following a full explanation of the nature and purpose of the study, by signing the informed consent form approved by the Institutional Ethics Committee (IEC) prior to all evaluations.

The investigator will maintain a screening log (appendix 3) on all patients considered for inclusion into the study in the Investigator Site File

### **9.3 Patient Exclusion Criteria**

Patients will not be considered for participation in the study if any of the following criteria listed below apply:

- Patients of ASA-class  $> III$
- Heart failure defined as NYHA class  $> 2$
- Aneurysm of the ascending and thoracic aorta
- Patients with Zenker's diverticle
- Local oesophageal disease (oesophageal stricture, oesophageal varices, previous oesophageal surgery in past 6 months before study inclusion, pharyngeal pouch)
- Patients receiving haemodialysis
- Patients with known bleeding diatheses
- Any bleeding disorder known from patient's history
- Patients with a haematocrit  $\leq 25\%$  despite pre-op transfusion

- Renal insufficiency (serum creatinine > 130 µmol/l or >1,5 mg/dl) or oliguria or anuria
- Impaired hepatic function described by decreased Quick-value < 60% or liver cirrhosis Child-Pugh C
- Additional contra-indications for either Tetraspan 6%, Tetraspan 10% and Sterofundin Iso are
  - hyperhydration state incl. lung oedema, generalized oedema, hypervolaemia
  - intracranial haemorrhage
  - hyperkalaemia, severe hypernatraemia or severe hyperchloraemia, hypercalcaemia
  - known hypersensitivity to HES or any of the excipients
- Pregnancy or lactation period
- Simultaneous participation in another interventional clinical trial (drugs or medical devices studies).
- Emergencies
- By judicial or enforceable order detained patients.

## 9.4 Stopping and Discontinuation Criteria

When the study in an individual patient is terminated, the nature of termination must be documented (scheduled end or premature termination/discontinuation). In the event of premature termination/discontinuation of the study, justification has to be given and it is to be recorded who took the decision to discontinue.

If the study as a whole is prematurely terminated or suspended, the concerned IEC and the regulatory authorities will be informed promptly and provided with the reasons for the termination or suspension by the sponsor.

### 9.4.1 Discontinuation Criteria Related to the Study

Criteria for discontinuation / termination of the entire clinical study include (not exclusively)

- Unexpected high frequency of serious adverse reactions during the study (frequency as outlined in SmPC will serve as a basis).
- Occurrence of a suspected unexpected serious adverse reaction which does not justify a continuation of the study
- Patients cannot be recruited in sufficient numbers. Not sufficient is defined as recruitment of less than 4 patients per month on average in all participating centres.

If after pilotphase (after 60 patients) the calculation of the pooled variance reveals that the estimated total number of 228 patients will be exceeded the study will not be carried on but stopped for futility after the pilot phase (see section 16).

### 9.4.2 Discontinuation Criteria Related to the Study Site

Discontinuation of the clinical study in an individual study site may occur because of various reasons including

- Failure of Investigator to comply with the ICH-GCP and/or applicable regulatory requirements.

- Submission of knowingly false or incomplete information from the site to B|Braun Melsungen AG, Study Monitor, or the authorities.
- Repeated non-adherence to protocol requirements including insufficient data quality (missing data in case report forms (CRFs) occurring repeatedly)
- Failure of the Investigator at a site to enrol patients into the study at an acceptable rate, i.e. less than 9 patients per 3 months.
- Personnel change without appropriate information to the sponsor.

#### 9.4.3 Discontinuation Criteria related to the Patient

The patients will be advised in the Informed Consent Forms that they have the right to withdraw from the study at any time without prejudice, and may be withdrawn at the Investigator's / Sponsor's discretion at any time, when this is considered to be in the interest of the patient.

Withdrawal of individual patients from treatment or from the study respectively could be caused by the following reasons (not exclusively):

Withdrawn by the Investigator due to

- Adverse Event, Serious Adverse Event (including pregnancy), e. g. hypersensitivity to HES, clinical significant abnormal laboratory value(s) such as hyperkalaemia (> 5,8 mmol/l), severe hypernatraemia (> 155 mmol/l) or severe hyperchloraemia (> 125 mmol/l), hypercalcaemia (> 2,8 mmol/l)
- The haemodynamic monitoring for guiding the application of the study drugs cannot be established.
- Protocol deviation or failure to comply with the protocol (e.g. dosing regimen, administration of an excluded medication, surgery performed as explorative laparotomy/premature termination of surgery)
- Subsequent occurrence of an exclusion criterion

which leads to inacceptance of further remaining either on treatment or in the study as considered by the investigator.

The patient requested withdrawal due to:

- An Adverse Event for which the Investigator did not consider removal from the treatment/study necessary
- Perceived insufficient therapeutic effect
- Perceived sufficient therapeutic effect
- Withdrawal of consent

In case a patient does not reappear to any scheduled visit (i. e. is lost to follow-up) reasonable effort should be made to contact this patient in order to complete assessments and/or to evaluate reason for non-appearance (possibly implicit withdrawal of consent).

In the event that a patient withdraws consent or is withdrawn from the *study*, the study termination page in the CRF should be completed indicating that the study was prematurely terminated. The Investigator should record the date of the withdrawal, the person who initiated withdrawal and the reason for withdrawal.

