### **10.2.3 Duration of treatment**

Treatment with Investigational Product starts after reliable basal oesophageal Doppler measurements are obtained and before skin incision.

After final positioning of the patient in the operating theatre the oesophageal probe will be placed and basal measurements will be recorded after correct placement of probe and reliable measures are obtained. Thereafter, before skin incision, the first bolus of Investigational Product of 250 ml/5 min will be given and the algorithm of the individualized volume replacement therapy is initiated. Oesophageal Doppler guided volume replacement will be performed throughout surgery.

Treatment with Investigational Product ends with surgery when the oesophageal probe is withdrawn. In case all bottles of Investigational Product as compiled by the pharmacist are used up before end of surgery then open-label treatment (in addition to basal balanced crystalloid infusion) with a balanced crystalloid (Sterofundin ISO) will be performed from then on during surgery.

After surgery, on ICU, volume replacement will be performed at the discretion of the attending physician. In case colloidal volume replacement is required on ICU on the day of surgery no HES-product but other colloidal volume replacement (e. g. gelatine) will be used. All volume/fluid replacement therapy will be recorded (separately for colloids and crystalloids).

(Note: The loading of the epidural catheter and start of continuous epidural analgesia will be performed at the end of surgery after all intraoperative, study-related measurements have been finalized.)

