### Handling missing data and outliers

Every effort will be made to collect all data points in the study. The amount of missing data will be minimized by appropriate management of the randomized, prospective, trial, proper screening of subjects, and training of participating investigators and other authorized staff (e.g. nurses), monitors and study co-ordinator. Since all patients who are randomized will be included in the primary analysis, in those instances where data are missing, missing values will not be imputed.

Missing data in tables and listings will be handled as missing data by inserting the symbol '.

Outliers may be identified using stem-leaf plots and frequency distributions, Scatter and box plots may be also generated for outlier identification. For normally distributed data, values more than three standard deviations away from the mean will be considered outliers. Transformation of the data to mitigate the influence of outliers may be considered. If outliers remain, additional analyses excluding these values will be done and discussed in the report.

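### Section 9.4.3 does not separate stopping the product from leaving the study, so a postoperative withdrawal by the investigator can end outcome collection for reasons that overlap with the trial's own outcomes

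*Protocol*

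**What the plan says.** Section 9.4.3 opens its list with "Withdrawal of individual patients from treatment or from the study respectively could be caused by the following reasons (not exclusively", so one set of reasons serves both decisions. The investigator's reasons begin with "Adverse Event, Serious Adverse Event (including pregnancy), e. g. hypersensitivity to HES, clinical significant abnormal laboratory value(s" and continue with failure to establish the haemodynamic monitoring, protocol deviation and "Subsequent occurrence of an exclusion criterion". A closing clause, "which leads to inacceptance of further remaining either on treatment or in the study as considered by the investigator", leaves both the decision and its extent to the investigator.

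The exclusion criteria in section 9.3 include serum creatinine above 130 µmol/l "or oliguria or anuria", haemodialysis, lung or generalised oedema, and hypervolaemia.

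On exposure, section 10.2.3 states: "Treatment with Investigational Product ends with surgery when the oesophageal probe is withdrawn".

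On what follows, a patient who "is withdrawn from the *study*, the study termination page in the CRF should be completed indicating that the study was prematurely terminated" also has the date, initiator and reason recorded. Section 9.4.3 mentions completing assessments only for patients who miss a scheduled visit and are lost to follow-up.

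On analysis, section 16.8 makes the intent-to-treat or full analysis set primary. The missing-data text in section 16.5 begins "Since all patients who are randomized will be included in the primary analysis" and rules out imputation.

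**The concern.** Some of the later exclusion criteria are also what the trial measures. Renal function is a secondary objective (section 7.2). Creatinine, urine output and extravascular lung water are safety variables (section 12.2). A patient who becomes oliguric or oedematous on day 2 therefore has a study outcome and, at the same time, a permitted reason to leave the study.

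By then the infusion is over, so leaving protects the patient from no product and removes only the later observations. The second primary endpoint, time until fully on oral diet, is followed for up to 15 days and is the most exposed. Renal and other safety outcomes and the 3-month EQ-5D are exposed in the same way.

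If such withdrawals are related to slow recovery and differ between the two HES arms, the arm that loses more slow patients looks faster. No analysis plan can recover values that sites were allowed to stop collecting.

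**Working it through.** **1. What survives withdrawal from the study**

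| Assessment | Where scheduled | Stated to continue after study withdrawal? |
|---|---|---|
| Diet check to day 15 | Sections 11 and 14.1 | No |
| Serum creatinine, days 3 and 7 | Sections 12.2 and 14.1 | No |
| Adverse events to day 5; unresolved SAEs to study end | Sections 12.2 and 13.3 | General rule; withdrawn patients not mentioned |
| Complications, at study end | Section 12.3 | General rule; withdrawn patients not mentioned |
| EQ-5D at 3 months | Sections 12.3 and 14.1 | No |

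A patient withdrawn before reaching full oral diet has no value for the second primary endpoint. With no imputation, that patient cannot contribute, whatever the analysis set is called.

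**2. The protocol's own figures for the second primary endpoint (section 16.4)**

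Inputs: difference 1.5 days, effect size 0.698, 69 per group, two-sided 5%.
- Implied SD = 1.5 / 0.698 = 2.15 days.
- Noether's formula: p = Φ(0.698/√2) = 0.689. The number per group for 80% power is (1.960 + 0.842)² / [2 × 3 × (0.689 − 0.5)²] = 36.5, so 37.
- Power at 69 per group: Φ(√(2 × 69 × 3) × 0.189 − 1.960) = 97.1%.
- With drop-out: 69 × 1.10 = 75.9, so 76.

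The stated 37, 97% and 76 all reproduce. No sample-size figure is disputed.

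**3. Worst-case shift in one arm**

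If an arm loses exactly the slowest fraction q of a normal distribution, its mean falls by SD × φ(z) / (1 − q), where z is the upper-q point. This gives 0.23, 0.42 and 0.59 days for q = 5%, 10% and 15%. The 10% case is 0.42 / 1.5 = 28% of the planned difference.

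**4. Range when withdrawal is only partly related to the outcome**

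Assumptions: 76 randomised per arm, normal times with SD 2.15 days, no true difference, and a two-sided 5% Mann-Whitney test on the patients who remain. The withdrawn patients are those highest on a latent score whose correlation with time to diet is varied. Of 76 patients, 10% is taken as 8 and 5% as 4. Each entry uses 20,000 simulated trials and shows the false difference in days, then the rejection rate.

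| Correlation | 10% vs 0% | 10% vs 5% | 10% vs 10% |
|---|---|---|---|
| 1 (exactly the slowest) | 0.42; 19.6% | 0.19; 10.6% | 0.00; 8.0% |
| 0.7 | 0.30; 13.0% | 0.13; 7.7% | 0.00; 6.4% |
| 0.5 | 0.22; 9.2% | 0.09; 6.2% | 0.00; 5.4% |
| 0.3 | 0.12; 6.4% | 0.06; 5.4% | 0.00; 5.2% |

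With zero correlation every scenario returns about 5%. The last column is a control. Equal loss causes no bias in the mean, yet cutting off exactly the slowest patients still lifts rejection to 8.0%. Part of the 10.6% for 10% vs 5% at correlation 1 is therefore an artefact of exact trimming and not an effect of differential loss.

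**The case against.** **Withdrawal is discretionary.** Section 9.4.3 says that the reasons could lead to withdrawal, and it ties investigator or sponsor withdrawal to the patient's interest. Stopping bedside diet checks in an inpatient hardly serves that interest. The section also distinguishes study from treatment, because the termination page applies only to the former. This stands: a reader might infer that bad outcomes do end data collection, but the text only permits it. What is missing is an assignment of reasons to the two decisions and a statement on continued collection.

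**Other sections point towards retention.** Adverse events are followed through the trial (section 13.3), unresolved serious events to study end (section 12.2), and complications that delay oral nutrition are documented (section 12.3). Section 13.2.1 removes many expected perioperative deviations from the adverse-event definition. This narrows the gap for safety. None of these rules says that it applies after study withdrawal, and none covers the diet check, creatinine on days 3 and 7 or the EQ-5D.

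**Not every exclusion criterion can arise later.** A reader might add low haematocrit or coagulopathy to the examples. The haematocrit criterion refers to preoperative transfusion, so it does not newly arise after surgery. The bleeding criteria concern known or historical disorders, and a low Quick value appears only as a marker of hepatic impairment. An acquired coagulopathy could enter only through the adverse-event or laboratory reason. Creatinine, oliguria or anuria, and oedema remain valid examples.

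**The first primary endpoint is safe, and the second is gated.** Intraoperative HES volume is fixed when surgery ends. The second endpoint is tested only if the first is significant (section 16.1), so the rejection rates above apply once that gate is passed.

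**Analysis sets are left to the analysis plan.** Section 16.8 says so, and that plan is not at hand. It therefore cannot be concluded that the promised intent-to-treat analysis will not be delivered, only that the protocol does not secure the data for it.

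**Conclusion.** The concern holds as a gap in the protocol's data-collection rules. Section 9.4.3 permits study withdrawal after surgery for reasons that overlap with renal and fluid-overload outcomes. Such a withdrawal can only lose data, and no section keeps the key outcomes going. The loss would fall on the second primary endpoint, on renal and other safety outcomes, and on quality of life.

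The size is uncertain. The 10% drop-out allowance in section 16.4 shows that losses of this order are planned for, but it says nothing about cause or arm. At an assumed 10% against 0% withdrawn, the false difference is about 0.1 to 0.4 days against a planned 1.5, and rejection is about 6% to 20% against a nominal 5%. At 10% against 5%, rejection is about 5% to 11%, partly artefact at the upper end. The upper figures require that the withdrawn patients are exactly the slowest, and should be read as bounds.

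**What to change.** Amend section 9.4.3 to treat stopping Investigational Product and ending data collection as two decisions. State that, unless the patient withdraws consent to follow-up, every randomised patient, including one withdrawn by the investigator, continues these assessments and is analysed as randomised:
- the diet check to day 15;
- serum creatinine on days 3 and 7;
- adverse-event, serious adverse-event and complication recording;
- the 3-month EQ-5D.

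Burdensome study-only measurements such as PiCCO may stop, so the investigator keeps room to act in the patient's interest. Restricting all study withdrawal to withdrawn consent would be broader than needed. The clinical grounds for stopping the infusion are left as they are. The termination page should record which of the two decisions was taken.

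The cost is a short amendment, a small CRF change and a few more pages for withdrawn patients. Every assessment listed is already scheduled.
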